### Motor activity, distal temperature, and digital biomarker registration—actigraphy

A research-grade ambulatory wristband (Empatica E4) [71] with sensors that register accelerometric data, peripheral body temperature, electrodermal activity, and photoplethysmography (PPG) [82–84] is applied. PPG employs infrared light to gauge volumetric changes in blood circulation, making it a widely used method for estimating heart rate and obtaining pulse oximetry readings [85, 86]. Heart rate variability analysis displays the function of the autonomic nervous system, and mood disorders are linked with autonomic dysfunction [87]. Autonomic activity can furthermore be assessed by observing electrodermal activity (skin conductance), which measures sweating on the skin, a function regulated by the sympathetic branch of the autonomic nervous system [88]. Accelerometry measures motor activity, with recordings of acceleration in three-dimensional space over time. The information in motor activity is hypothesized to be an objective observation of the inner physiological state [89]. Variations in energy-levels and activation patterns provide information about mood state, as well as circadian rhythmicity, which seems disrupted in depression [90, 91]. Additionally, the peripheral body temperature also expresses circadian rhythmicity [92]. These data will be acquired over a 48-h period to assess the circadian effects of the heart, electrodermal activity, motor activity and body temperature.

### Blood sampling and biobank

Blood samples will be stored in a study-specific biobank at Biobank Haukeland. If the study participants also provide informed consent for prolonged storage of the samples, the material will be transferred to the ECT research biobank (“*Forskningsbiobanken for nevrostimulerende behandling i Helse Vest*”, Regional Comittee for Medical Research Ethics Western Norway (REK West) 2017/925) after the termination of the study. We will collect blood in serum tubes, whole blood in EDTA tubes (Ethylenediaminetetraacetic acid), and PAX-gen tubes (for stabilization of intracellular RNA) for each timepoint. In the automated biobank the serum will be aliquoted in 6 × 260 µl tubes. The EDTA whole blood will be aliquoted and stored in 3 × 2 ml. The samples in PAX-gen tubes will be stored as is.

### Power analysis

Based on a previous study [93], the first hypothesis of this protocol is that baseline global cerebral blood flow (CBF) will separate responders (lower CBF) from nonresponders at a threshold of ~ 45 mL/100 g/min, and that CBF will increase with ECT. The sample size needed to detect a difference at baseline between responders and nonresponders based on the data in Fig. 1 in [93] is 14 per group (1- β = 0.8, α = 0.05). Detection of a treatment-induced change in the regional hippocampal CBF (paired t test) will require a sample of 22 patients. Our sample of 50 patients should be adequate.

Very large sample sizes are needed to boost statistical power and close knowledge gaps (e.g., confirm or refute results from small studies) and to utilize machine-learning tools for outcome prediction. Hence, team science efforts are important, and parts of the analysis will be achieved through data sharing and collaboration with consortia such as the Genomics of ECT International Consortium [94](Gen-ECT-ic) and GEMRIC [77].

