#### Study design

The study is a prospective pre-post longitudinal case–control observational and “naturalistic” study, i.e., we will collect data from patients who receive the standard clinical treatment and compare three groups: patients receiving ECT, patients receiving TMS, and healthy controls who do not receive any treatment (Fig. 1). The data collection is broad and comprehensive. This is necessary due to the lack of knowledge in the field; exploratory and hypothesis-generating research is important and warranted.

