**Fig. 1 Fig1:**
[figure not shown]
Study flow-chart. Assessments are performed at multiple time points before, during and after treatment as illustrated. CA, Core Assessment (includes neurocognitive tests, actigraphy and for the patient groups clinical assessment)

MRI, blood samples, neuropsychological assessments (including spatial navigation – a function residing in the hippocampus), clinical scales and depression scores from 100 patients in a major depressive episode will be collected. The ECT (*N* = 50) and TMS (*N* = 50) study groups will be followed over 5 time points (TP): baseline (TP1), during (after 1^st^ (TP2) and 6^th^ ECT or 10^th^ TMS (TP3)), after treatment series (TP4), and at 6 months follow-up (TP5). Healthy controls (*N* = 50) will be assessed at four time points (corresponding to TP1, TP2, TP4 and TP5 to estimate variance due to noise, and to control for effects of time. There are comprehensive and in-depth assessments of participants, spanning from diagnosis, history and imaging to neuropsychological profiling, blood biomarkers, genetics, and epigenetics (see Fig. 1 and Table 1).

**Table 1 Tab1:** Variable overview

	Timepoints (TP) for analyses	TP1		TP2	TP3	TP4	TP5
	Timepoints relative to treatment	Baseline, before treatment		During treatment		After treatment	
	Timeframe for each test	< 7 d of first ECT/TMS	1–2 h before first ECT/TMS	1–2 h after first ECT/TMS	before 7th ECT/11th TMS	7–14 d after last ECT/TMS	6 mo after ECT/TMS series
Clinical assessments ^c^	Clinical examination	x					
ECT- stimulus specific measures ^b^	EEG, pulse width, charge, amplitude, frequency, pulse train duration, seizure duration, electrode placement and reorientation time		x		x		
	Current and concomitant medication	x			x	x	x
Symptom severity ^c^	MADRS [47]	x			x	x	x
	BDI [48]	x			x	x	x
	CGI [49]	x			x	x	x
	EMQ [50]	x			x	x	x
	MMSE [51]						
Radiology	MRI: T1, T2, MRS, ASL, DWI, rsfMRI		x	x	x	x	x
Neurocognitive assessments aligned with GEMRIC recommendation	1. RAVLT [52, 53]	x				x	x
	2. Phonemic Fluency [54]	x				x	x
	3. Semantic Fluency [54]	x				x	x
	4. SDMT [55]	x				x	x
	5. TMT A + B [54]	x				x	x
	7. DSB [55]	x				x	x
	8. AMT [56]	x				x	x
	9. MoCa version 7.1 [57]	x				x	x
	10. NART [58]	x				x	x
	11. QIDS-SR 16 [59]	x				x	x
Study specific neurocognitive assessments	1.VAMS^a^,^c^ [60]	x				x	x
	3. Spatial navigation: Memory retrieval task [61, 62], Four Mountain [63], Sea Hero [64]	x				x	x
	4. RCFT [65]	x				x	x
	5. CWIT [54]	x				x	x

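### The hippocampal blood-flow change attributed to treatment is sized on a patients-only paired t test, although 50 controls are scanned to separate time effects from treatment effects

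*Protocol article*

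**What the plan says.** The Power analysis section gives the first hypothesis two parts: baseline global CBF separates responders from nonresponders, "and that CBF will increase with ECT". The first part is sized at 14 per group with "1- β = 0.8, α = 0.05". For the second part the section states: "Detection of a treatment-induced change in the regional hippocampal CBF (paired t test) will require a sample of 22 patients". It concludes: "Our sample of 50 patients should be adequate". It does not mention the controls, and it prints no mean change, SD of change or standardised effect for the 22.

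The Study design section says that the study will "compare three groups: patients receiving ECT, patients receiving TMS, and healthy controls who do not receive any treatment". The text under Fig. 1 has the 50 controls assessed at four time points (TP1, TP2, TP4 and TP5) "to estimate variance due to noise, and to control for effects of time". In Table 1 the imaging row, "MRI: T1, T2, MRS, ASL, DWI, rsfMRI", does not carry the footnote that marks assessments omitted in controls. So, as far as the article shows, controls have the same perfusion scans.

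**The concern.** A patients-only paired t test asks whether mean CBF after treatment differs from mean CBF before it. Anything that moves CBF between two scans weeks apart enters the answer: scanner drift, familiarity with the scanner, the passage of time. The sizing sentence nevertheless attributes the change to treatment. The data that would separate these shared effects from an ECT effect are being collected, but the named test does not use them.

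Two things are at stake. First, a significant paired test could be read as confirming part of the first hypothesis without the comparison that the design provides. A larger sample does not cure this; it makes a small drift easier to declare significant. Second, setting 22 beside 50 suggests a wide margin, and the controlled comparison has a narrower one.

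The region is also left open. The increase clause speaks only of CBF, while the sizing is for the hippocampus, so a reader cannot tell which measurement decides the hypothesis.

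**Working it through.** **Inputs from the protocol article.** Paired t test, n = 22; 50 patients called adequate; 50 in each of the three groups (Power analysis; text under Fig. 1). Alpha 0.05 and power 0.80 are printed for the responder comparison one sentence earlier.

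**Assumptions.** Alpha and power carry over to the paired test, which is two-sided. Controls have the same SD of change as patients and no mean change. The article gives none of these, so ranges follow.

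**Step 1: the stated 22.** It cannot be reproduced forward, because no effect or SD is printed. Inverted with the exact noncentral t distribution, a paired test with n = 22, two-sided 0.05 and power 0.80 implies a standardised change dz = mean change / SD of change = 0.626. The normal approximation gives (1.960 + 0.842)/√22 = 0.597, and a one-sided exact test gives 0.548. At dz = 0.626 the paired test has 99% power with 50 patients.

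**Step 2: same effect, tested against controls.** With equal SDs of change, the difference in mean change has variance 2·SD²/n, so n per group ≈ 2(1.960 + 0.842)²/0.626² = 40.0. The exact two-sample t calculation gives 40.99, so 41 per group. Other conventions (one-sided, normal approximation, 22 rounded up from just above 21) give 38 to 44.

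**Step 3: power of the controlled test at dz = 0.626.**

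| Completers per group | Power |
|---|---|
| 22 | 53% |
| 40 | 79% |
| 41 | 80% |
| 45 | 84% |
| 50 | 87% |

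Power stays at 80% until about 18% per group lack a usable pair of scans (50 × 0.82 = 41).

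**Step 4: sensitivity to the unknown control values.**

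| Control SD of change ÷ patient SD | n per group, normal approximation |
|---|---|
| 0.5 | 26 |
| 0.75 | 32 |
| 1 | 41 |
| 1.25 | 52 |

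The formula is (1 + ratio²)(1.960 + 0.842)²/0.626², rounded up.

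| Control mean change as share of patient change (same direction) | n per group | Power at 50 per group |
|---|---|---|
| 0 | 41 | 87% |
| 10% | 51 | 80% |
| 20% | 64 | 70% |
| 30% | 83 | 58% |

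**Step 5: what the paired test does when treatment has no effect.** As an illustration with assumed drifts, suppose time and rescanning alone move CBF by 0.2 or 0.3 SD of change. The paired test in 50 patients then rejects 28% or 55% of the time, against a nominal 5%.

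**The case against.** The strongest reply is that the protocol's conclusion survives. On the figures above, 50 per group covers the controlled test with about 87% power. Falling to 79% takes a 20% loss that the article nowhere states. That stands: the sample is not shown to be too small, and no added enrolment follows.

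Second, a sizing sentence in a condensed article is not an analysis plan, and the three-group comparison is already in the design. That stands in part. One cannot conclude that the controlled comparison will be omitted. But the article did not leave the matter open: it names a test and attributes the change to treatment, and that test cannot support the attribution.

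Third, 41 cannot be read from the document. That stands too. A reader might infer that the trial requires 41 per group and that 22 is an arithmetic error. The document supports neither: 22 may be correct for the test it names, and 41 holds only under the stated assumptions. It also sizes a comparison of change scores, so it should not be attached to an analysis that adjusts for baseline. Such adjustment is itself contestable here, because the groups are not randomised and patients may differ from healthy controls at baseline.

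Fourth, healthy controls have no depressive episode and receive no anaesthesia. They cannot remove regression to the mean, spontaneous improvement or anaesthetic effects. This limits what the contrast can show, but it remains less biased than having no control.

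Finally, a reader might see a contradiction between global and hippocampal CBF. The word global belongs to the baseline clause; the increase clause names no region. The sizing is narrower than the hypothesis and does not contradict it.

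**Conclusion.** The point holds as a mismatch between the claim and the test sized for it. A change attributed to treatment is sized on patients alone, while controls are followed over the same period partly to account for time. It is worth correcting, but it does not threaten the study's size. If 22 reflects 80% power at two-sided 0.05, and controls have the same SD of change and no mean change, the controlled test needs about 41 per group, and the planned 50 gives about 87% power. The margin is thinner than 22 against 50 suggests. It is used up if about 18% per group lack paired scans, if control variability is clearly above that of patients, or if controls show about 10% of the patient change. The size of any real drift is unknown from the document, so the false-positive rates in step 5 show the mechanism and are not estimates for this study.

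**What to change.** - Test the CBF-increase hypothesis as the ECT-versus-control difference in change from TP1 to TP4 (the group-by-time term), and keep the within-patient paired test as descriptive.
- Name the one region, global or hippocampal, that decides the hypothesis.
- Restate the sizing with its assumed mean change, SD of change, alpha, power and sidedness. If the source values match those back-solved here, the text could read: about 41 per group under equal SD of change and no mean change in controls; 50 per group gives about 87% power, and 40 completers per group about 79%.
- State that the contrast controls for time and scanning effects only, and that healthy controls do not remove regression to the mean or spontaneous improvement.

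The cost is rewording and a less favourable figure than 22. No new data or participants are needed. The Discussion reports 11 ECT patients and 12 controls included at submission, so the change can be made early.

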## Discussion

The study described in this protocol will provide a comprehensive dataset with opportunity for multiple future analyses that can cast light on the mechanisms of action for ECT and TMS. At the time of submission of this manuscript, the study included 11 ECT patients, 10 TMS patients and 12 healthy controls. We will explore the underlying mechanisms for both the therapeutic and adverse effects of ECT and TMS. Our translational goal is to select the right patients for treatment, also addressing the primary concerns of our patient representatives who ask for personalized recommendations with respect to the likelihood of good outcome versus cognitive side effects. Ultimately, knowledge from the project should also be communicated broadly to inform the public, in order to dispel remaining myths and stigma, surrounding ECT.

### Hypotheses

#### The response to ECT/TMS can be predicted by (low) pretreatment CBF

Neuroimaging studies found abnormal brain functioning in depression [95, 96]. Although several machine-learning algorithms for predicting treatment outcome based on functional [97] or structural [34, 98, 99] neuroimaging have been developed, to date, none of these algorithms have been translated to clinical practice. Hence, a broad approach including novel methods to tackle the prediction challenge is warranted. A promising recent study found that (CBF) before treatment could distinguish responders (lower global CBF) from nonresponders by using ASL-MRI [93]. We hypothesize that responders will have lower pre-ECT global CBF than nonresponders.

By using ASL-MRI, absolute CBF can be estimated without use the of contrast agent – making eventual clinical implementation affordable and free from the risks associated with intravenous injection of gadolinium contrast.

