### Clinical assessments

The clinical assessment will be performed in accordance with standard clinical protocols at the treatment unit. This includes electroencephalography (EEG), ECT stimulus specific variables (e.g., pulse width, charge delivered, amplitude, frequency, pulse train duration, seizure duration and electrode placement), reorientation time, and anesthetic used for induction. Weekly clinical assessments will include the MADRS [47], Beck Inventory test (BDI) [48], Clinical Global Impression Scale (CGI) [49], Mini Mental Status (MMSE) [51] and Everyday Memory Questionary (EMQ) [50]. Psychiatric history and the cause for cessation of ECT will be recorded. Response to treatment will be defined as > 50% reduction in MADRS score, and remission as a MADRS score ≤ 10.

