### Research questions

In addition to the two primary hypotheses, several analyses can be performed that can shed light on the mechanisms of action suggested by the DPR hypothesis.

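### The first primary hypothesis tests baseline CBF against a responder/nonresponder split of MADRS, giving up about 36–46% of the information if 50–75% respond; analyse the MADRS score instead

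*Protocol article*

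**What the plan says.** The Hypotheses section states "We hypothesize that responders will have lower pre-ECT global CBF than nonresponders". The Research questions section gives this primary status: "In addition to the two primary hypotheses, several analyses can be performed".

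Clinical assessments defines the two classes: "Response to treatment will be defined as > 50% reduction in MADRS score, and remission as a MADRS score ≤ 10".

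Power analysis uses the same two-group form. It expects CBF to separate responders from "nonresponders at a threshold of ~ 45 mL/100 g/min". The number needed "is 14 per group (1- β = 0.8, α = 0.05"), and this is "based on the data in Fig. 1 in [93"]. The conclusion is "Our sample of 50 patients should be adequate". The article itself gives no mean difference, standard deviation or responder share.

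Table 1 lists MADRS for patients at TP1, TP3, TP4 and TP5, with TP4 falling 7–14 days after the last treatment. The score before and after treatment is therefore already collected.

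**The concern.** Both variables in this hypothesis are measured on a scale, but the hypothesis and its sample size reduce the outcome to two classes. Patients just either side of a 50% reduction count as opposites, and all differences within a class are ignored.

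The rule can also order patients oddly. Entry requires MADRS of at least 25 (Inclusion criteria). A fall from 50 to 24 is 26/50 = 52% and counts as response. A fall from 26 to 13 is exactly 50% and does not, although that patient ends far less ill.

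At stake is the power of a primary test that aims to confirm one earlier study. If the true association is weaker than in that study, the split makes a null result more likely and harder to interpret.

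**Working it through.** **Inputs from the protocol.** 14 per group, power 0.80, α 0.05, 50 patients (taken here as the ECT group, all with TP4 MADRS).

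**Assumptions.** Two-sided test, since sidedness is not stated. Approximately normal outcome. Responder share p of 50–75%. The only nearby figures in the Background are ECT remission of up to 75% and about two-thirds responding to TMS; neither is a planning value for ECT response.

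**1. The plan's own figure.** The 14 per group cannot be reproduced forwards, because no difference or SD is given. Solved backwards:

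- Normal approximation: d = (1.960 + 0.842) × √(2/14) = 1.06.
- Noncentral t: d = 1.10.
- One-sided: 0.94 (normal) or 0.97 (t).

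The planning effect is therefore a standardised difference of about 1.1.

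**2. Information kept by the split.** For a normal outcome cut so that a share p responds, the efficiency relative to the uncut outcome is φ(z_p)² / [p(1 − p)].

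| Responder share | Efficiency | Loss | 50 patients worth |
|---|---|---|---|
| 50% | 0.637 | 36.3% | 31.8 |
| 2/3 | 0.595 | 40.5% | 29.7 |
| 75% | 0.539 | 46.1% | 26.9 |

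Outside this range the loss is 42.4% at 30% responders and 51.0% at 80%.

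**3. Power of the split comparison in 50 patients.** Noncentral t, noncentrality d × √(n₁n₂/50), two-sided 0.05.

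| Split | d = 1.10 | d = 0.7 | d = 0.5 | d for 80% power |
|---|---|---|---|---|
| 25/25 | 96.8% | 67.9% | 41.0% | 0.81 |
| 33/17 | 95.1% | 63.2% | 37.5% | 0.85 |
| 38/12 | 90.2% | 54.4% | 31.6% | 0.95 |

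**4. The same effects as correlations.** The point-biserial correlation is d√[p(1 − p)] / √[1 + d²p(1 − p)]. Dividing it by the square root of the efficiency gives the underlying correlation ρ.

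- d = 1.10, p = 0.5: 0.55/√1.3025 = 0.482; 0.482/0.798 = 0.60 (0.59 at p = 0.75).
- d = 0.7, p = 0.5: 0.35/√1.1225 = 0.330; 0.330/0.798 = 0.41.
- d = 0.5, p = 0.5: 0.25/√1.0625 = 0.243; 0.243/0.798 = 0.30.

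**5. Continuous against split outcome, n = 50.** Fisher z: power = Φ(atanh(r) × √47 − 1.96), with r = ρ for the continuous outcome and r = ρ × √efficiency for the split.

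| ρ (assumed) | Continuous | Split, 50% to 75% responders |
|---|---|---|
| 0.3 | 56% | 39% to 34% |
| 0.4 | 83% | 62% to 55% |
| 0.5 | 97% | 83% to 75% |

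These are for a simple correlation. If ρ is read as the partial correlation given baseline MADRS, √47 becomes √46. Power at ρ = 0.4 is then Φ(0.4236 × 6.782 − 1.96) = Φ(0.91), about 82%.

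**The case against.** **The binary form is deliberate.** The test replicates an earlier result in the same form, and the long-term aim is a personal probability of a good outcome (Aim of the study). Response is defined in advance, and nothing in the article contradicts itself here or rules out a continuous analysis as well. This stands as a reason to keep the responder comparison. It is not a reason to rest the main test on it, and the second primary hypothesis is already framed as a correlation.

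**A reader might infer that the study is underpowered.** The documents do not support that. At the effect implied by 14 per group, the split comparison keeps about 90–97% power. The loss matters only if the true effect is smaller. That is plausible, since a ρ of about 0.60 is large for a single baseline marker and comes from a figure in one study, but it is not shown.

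**A reader might also infer that the comparison is unadjusted and open to confounding by age and sex.** That does not follow. No test or covariate set is named for this comparison; the one test named in Power analysis is the paired t test for change in hippocampal CBF. Silence in a condensed article is not a decision to leave covariates out. The documents also say nothing about whether CBF depends on age or sex, which appear only in the matching of healthy controls.

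**The gain is calculated under normality.** TP4 MADRS is bounded below. If many patients remit, scores will bunch near the floor and the gain could be smaller than shown. This stands.

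**Conclusion.** The point holds as a matter of efficiency. The hypothesis and its sample size are fixed on a split of a score that the study already collects. The loss is about 36–46% of the information, conditional on approximate normality and 50–75% responders.

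The practical consequence depends on the true effect: little at d of about 1.1, and material at 0.5–0.7, where the split has roughly 32–68% power. At an assumed ρ of 0.4, close to d = 0.7, the continuous outcome would have about 83% against 55–62% for the split under the same approximation. The responder shares and these smaller effects are assumptions, not protocol figures. The formula also treats the analysed score and the variable that was cut as the same quantity, whereas response is cut on percentage reduction and the proposed outcome is TP4 MADRS given baseline.

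**What to change.** Name as the main test of the first hypothesis, in the ECT group, a linear regression of TP4 MADRS on baseline global CBF kept continuous, with baseline MADRS in the model. Report the CBF coefficient with its confidence interval.

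Keep the responder/nonresponder comparison and the threshold of about 45 mL/100 g/min as prespecified supportive analyses that replicate the earlier study. State in advance how the regression will be handled if TP4 scores cluster near zero.

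The cost is a change of analysis wording, with no new visits, measurements or patients. At submission 11 ECT patients had been included (Discussion), so the article describes an early stage of recruitment. The drawbacks are that the main result would no longer be in the earlier study's form, which the supportive analysis covers, and that a floor effect could shrink the gain.
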